**Parameters Assessed: Time Line**										
Pod = post operative day	**VISIT 1**	**VISIT 2**	Week 1	Week 2	Week 3	Week 4	Week 5	**VISIT 3**	**VISIT 4**	**VISIT 5**
	Enrolment (POD -2 wks)	Discharge from hospital (approx POD10)						Week 6	3/12 Clinic	6 / 12 Clinic
**Acceptable Variability**	**+/- 7 days**	**+/- 4 days**						**+/- 7 days**	**+/- 14 days**	
			**Intervention period – home feeding**							
Baseline Characteristics	**X**									
Weight (kg)	**X**	**X**						**X**	**X**	**X**
Height (m)	**X**									
Body mass index (kg / m^2^)	**X**	**X**						**X**	**X**	**X**
Anthropometrics	**X**	**X**						**X**	**X**	**X**
Mid arm circumference										
Anthropometrics	**X**	**X**						**X**	**X**	**X**
TricepSkinfold										
Thickness										
Anthropometrics	**X**	**X**						**X**	**X**	**X**
Grip strength										
Nutritional intake (3 day food diary)		**X**						**X**	**X**	**X**
Post-operative complications		**X**	Collected by Research/Community Dietitian Prospectively						**X**	**X**
Healthcare Resource use	X									**X**
Quality of Life EORTC	**X**	**X**						**X**	**X**	**X**
Quality of Life EQ-5D	**X**							**X**		**X**
Semi-structured interview	End of intervention period									
	Sample of up to 20 trial participants									

The University of Leicester Clinical Trials Unit has developed a trial-specific database. Data will initially be collected onto paper case reports forms and subsequently entered into the electronic database.

### Qualitative data

For those participants also recruited into the qualitative part of the study there will be one interview to take place at the end of the six-week intervention period. Interviews will be conducted in a private room with a member of the research team who has received communication skills and interview training. Interviews should take between 30 and 60 minutes. Following each interview the researcher will make field notes including any observations. This will help to inform reflexive reflection. The interview will be digitally recorded and then transcribed verbatim. Participants will be assigned a false name when the interview is transcribed and the recording will be destroyed when no longer needed for study purposes. To help inform the design of future research in this area, all participants will be asked to provide details of their experiences of being involved in a research trial, in particular the recruitment, randomization, and assessment processes. All participants will be asked on the consent form whether they consent to being contacted at the end of their involvement in the study to complete the questionnaire.

## Data analysis

### Quantitative data

As this is a pilot study and we aim to estimate a number of quantities necessary for the design and delivery of a definitive multi-centre trial, the estimates calculated will be presented along with 95% confidence intervals where appropriate. The proportion of eligible patients who consent to participate in the pilot will be calculated, along with the proportions in each intervention group completing six weeks and six months of assessments. Hospital readmission rates will be presented by intervention group. Variability of the QoL measures will be calculated, both by each group and pooled across both groups.

As it is anticipated that the likely outcome measure for the multi-centre trial will be QoL, a comparison of the QoL measure EORTC QLQ-C30 will be conducted using the Students t-test to compare the mean between the groups to provide a preliminary estimate of the treatment effect. Distribution of the data will be assessed graphically and if the normality assumption is considered to be unreasonable a non-parametric approach will be taken. A secondary analysis, using analysis of covariance (ANCOVA) and regression models will be conducted to adjust for type of surgery (used as a stratification factor in randomization) and baseline value of EORTC QLQ-C30.

The findings of the qualitative research may lead to a different outcome measure being proposed as the primary in the definitive trial and consequently the other QOL measures and other continuous outcomes at six weeks, three months, and six months will be analyzed similarly.

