### Sample size

Home JEJ feeding is not routinely carried out at present and there is no published data on the variables of interest in this patient population. Consequently the sample size in this pilot study was chosen to enable a sensible estimation of the quantities of interest, in particular variability, whilst not exposing too large a number of participants to the full range of experimental procedures.

We therefore aim to recruit 60 subjects, 30 randomized to home JEJ and 30 to treatment-as-usual, which (allowing for up to 17% early withdrawal) would result in 50 participants completing the 6-week intervention period.

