### Randomization

Participants are randomized to either the control or intervention group at enrolment, and prior to surgery, so that baseline QoL and nutritional parameters can be collected. We anticipate an early withdrawal rate due to perioperative mortality or morbidity of around 5% based on local experience. At the time of the operation it may not be clinically suitable to place a JEJ tube in all subjects, or some will not have a functioning JEJ tube (approximately 2%, due to kinking or blockage).

The randomized schedule is managed by the University of Leicester Clinical Trials Unit, using computer generated random assignment, using permuted block randomization, stratified for type of procedure (esophagectomy or total gastrectomy). A member of the research team (dietitian or lead clinician) will randomize the participant through an electronic Interactive Web Response System (IWRS). Participants are sequentially assigned to groups as they are entered into the study and the IWRS will provide a trial participation number.

Neither the study participants nor the research team are blinded to the allocation group. However the research dietician has no role in determining clinical care unless there are patient safety concerns. The research team did not consider it either ethical or practical to administer placebo feed to the control group.

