### Control

Participants randomized to the control group will continue to receive routine clinical care: JEJ feeds will be discontinued on day of discharge, the JEJ tube will remain in place until outpatient review in week six, and prior to discharge the participants will be taught how to flush the JEJ tube daily. Post-discharge dietetic follow-up will involve a routine telephone call and home visit from HENs within the first week of discharge. Additional HEN input will be dictated by nutritional need but will include at least one further contact within the six-week study period.

Following standard practice it may be considered necessary by the healthcare team to re-commence JEJ feeds which we anticipate may be the case in up to 15% of the control group. The criteria for recommencement of the feed will include the following: (1) more than 5% weight loss from baseline or hospital discharge value (visits 1 or 2), (2) clinical assessment by the managing team based on functional status (worsening dysphagia, exhaustion, or anorexia), or (3) oral energy intake reduced to one third of the estimated requirements.

In these situations, JEJ feeds will be restarted according to current practice (if necessary the patient will be readmitted to hospital). The trial participant will continue to be monitored following the trial schedule and the results will be analyzed on both an intention-to-treat and perprotocol basis. The only difference between the intervention and control arms will be the management and administration of the supplementary JEJ feeding for six weeks. All participants will receive clinical reviews following routine care from the multi-disciplinary team (MDT). It is likely that a small number of patients randomized to either group will require home jejunostomy feeding as part of their routine clinical care. These patients will continue feeding in accordance with their planned care. Consideration will be given to withdrawing the participant from the study where there has been major protocol deviation.

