### Health economics

An economic evaluation will be undertaken comparing the two groups to determine the cost-effectiveness of JEJ feeding. Patient questionnaires will be distributed to collect the cost to the NHS or personal social service and patient or carer cost. The main outcome for the cost utility analysis will be Quality Adjusted Life Years (QALYs) calculated from EQ-5D-3 L using linear interpolation and area under the curve methods. We will test the differences in QALYs calculated from EQ-5D values and EORTC QLQ-C30 measure of quality of life using the method described by McKenzie and van der Pol [29]. Results will be presented as incremental cost-effectiveness ratio (ICER) between the two groups.

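### The preliminary QoL effect comes from separate per-visit t-tests that ignore earlier EORTC scores, so it would be biased if health-related loss differs between the arms

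*Protocol article*

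**What the plan says.** Under Data analysis, Quantitative data, the protocol expects QoL to be the likely outcome of the multi-centre trial and plans that "a comparison of the QoL measure EORTC QLQ-C30 will be conducted using the Students t-test to compare the mean between the groups", to give a preliminary treatment effect. A non-parametric method replaces the t-test if normality looks unreasonable. ANCOVA and regression models, adjusting for procedure and baseline score, are secondary. Other QoL measures and continuous outcomes at six weeks, three months and six months are to be treated in the same way.

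Table 1 schedules the EORTC questionnaires at enrolment, discharge, week six, three months and six months.

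The Sample size section sets the number at 60, "allowing for up to 17% early withdrawal", so that 50 complete the six-week period. The Randomization section adds: "We anticipate an early withdrawal rate due to perioperative mortality or morbidity of around 5% based on local experience". Neither participants nor the research team are blinded.

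The Control section, discussing control participants who restart feeds, says "the results will be analyzed on both an intention-to-treat and perprotocol basis". The Health economics section says QALYs are "calculated from EQ-5D-3 L using linear interpolation and area under the curve methods".

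**The concern.** A t-test at one visit, run on observed scores, has nothing to say about a participant who has no score at that visit. The baseline ANCOVA leaves out the same people. Someone who leaves between discharge and week six has an EORTC score at enrolment and another at discharge. The second is the last measure of how that person was doing before home feeding began, and neither named analysis uses it. The same holds for the week-six score at three months, and so on.

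This matters because the QoL comparison is meant to inform the definitive trial. The arms are unblinded and differ in nutritional support at home, so it is plausible, though not shown, that people doing badly leave at different rates in the two arms. The difference among those observed would then mix the treatment effect with the pattern of loss.

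**Working it through.** **The plan's own figure.** 60 × (1 − 0.17) = 49.8, so 50 completing week six is reproduced. The allowance is 10 of 60 (16.7%). Perioperative mortality or morbidity at 5% accounts for 60 × 0.05 = 3 of these.

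**Bias in general terms.** If a fraction f of an arm is lost, and those lost score g SDs below those retained, the observed mean is too high by f × g SDs. The bias in the difference between arms is the difference of the two f × g terms. With 10 lost from two arms of 30, and g assumed to be 0.25 to 1.0 SD in both arms:

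| Split of the 10 lost | Bias formula | Size of bias (SD) |
|---|---|---|
| 5 and 5 | (5 − 5)/30 × g | 0 |
| 7 and 3 | (7 − 3)/30 × g | 0.03 to 0.13 |
| 10 and 0 | (10 − 0)/30 × g | 0.08 to 0.33 |

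**Bias with equal numbers lost but different reasons.** The documents give no SD, effect size or correlation, so these inputs are assumptions:
- QLQ-C30 SD 20 and true difference 5 points.
- Correlation ρ between visits 0.5 or 0.7.
- 17% lost in each arm, all between discharge and week six.
- Where loss depends on health, log-odds of loss = −1.88 − Z, where Z is the standardized discharge score. The constant is set to give 17%.

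Integrating over a standard normal Z, the mean of Z among those retained is 0.149. The observed week-six mean in that arm is therefore too high by ρ × 20 × 0.149:
- ρ = 0.5: 0.5 × 20 × 0.149 = 1.49
- ρ = 0.7: 0.7 × 20 × 0.149 = 2.09

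The ANCOVA and model columns come from a simulation with 1,000,000 per arm.

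| Loss depends on health in | t-test, ρ 0.5 / 0.7 | Baseline ANCOVA, ρ 0.5 / 0.7 | Model using enrolment and discharge scores |
|---|---|---|---|
| Controls only | 3.5 / 2.9 | 4.2 / 4.4 | 5.0 / 5.0 |
| Intervention only | 6.5 / 7.1 | 5.8 / 5.7 | 5.0 / 5.0 |
| Both equally | 5.0 / 5.0 | 5.0 / 5.0 | 5.0 / 5.0 |

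**Against sampling error.** With 25 per arm the standard error is 20 × √(2/25) = 5.66, and the 95% CI half-width is 2.01 × 5.66 = 11.4 points. The largest bias above is 2.09/5.66 = 0.37 of a standard error.

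**Variability.** Among those retained the SD is 19.7 (ρ = 0.5) or 19.5 (ρ = 0.7) instead of 20, so the SD estimate is hardly touched.

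**QALYs.** If d early deaths in an arm of 30 were omitted instead of scored 0, the arm's six-month mean would rise by about 0.5 × u × d/30, taking u as the mean utility of the others. With u assumed 0.6 to 0.8 and d from 1 to 3, this is 0.010 to 0.040.

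**The case against.** The strongest reply is that this is a missing-data rule, which a journal article may leave to the full protocol or SAP. That stands for imputation and for how deaths enter the QALYs. It does not dispose of the point, because the article does name the estimator and its time points, and that choice can be judged as stated.

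Several stronger readings are tempting, and the text does not support them:
- **That the intention-to-treat promise is broken.** The sentence is about control participants who restart feeds and are still followed. A t-test by allocated arm is compatible with it.
- **That the methods cannot handle loss, or use completers only.** Neither is stated. A t-test can follow imputation, and a per-visit test includes people who leave later.
- **That 17% is the expected loss.** It is an upper allowance.
- **That QALYs leave out the dead.** No such exclusion is written, and survival data are collected.

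The illustration also has limits. It is an extreme contrast, with loss tied to health in one arm and not at all in the other. It places all loss after discharge, whereas perioperative loss arises while both arms receive the same hospital care. Dropout was generated from the discharge score, so a model containing that score recovers the true value by construction. This shows what the scheduled data can repair if that is how people are lost, not that it is.

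The mention of regression models does not rule out a longitudinal model, but its stated purpose is adjustment for procedure and baseline.

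**Conclusion.** The point holds as a weakness in the stated analysis, not as a contradiction. The QoL effect comes from separate visit-by-visit comparisons that ignore intermediate scores already collected, in an unblinded trial that allows for up to 10 of 60 withdrawing early. Under the assumed inputs, one-sided health-related loss moves a true 5 points to about 2.9 to 3.5 or 6.5 to 7.1. The planned ANCOVA leaves roughly 0.6 to 0.8 points of this. Equal dependence gives no bias. These sizes rest on an SD, effect and correlations that the documents do not give, and they are small beside the roughly 11-point half-width of a preliminary estimate.

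A reader might infer that everything passed to the definitive trial is compromised. It is not: recruitment, retention and readmission are unaffected, retention counts the losses directly, and the SD barely changes. The handling of deaths in the QALYs is a matter to confirm, not an error shown in the text.

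**What to change.** Make the main QoL estimate a likelihood-based repeated-measures model by allocated arm, using all scheduled EORTC visits, with baseline score, procedure and arm-by-visit terms. Report the differences at six weeks, three months and six months with 95% confidence intervals, and state the number dead by each visit. Keep the per-visit t-test as a sensitivity analysis.

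For the QALYs, confirm in the plan that utility is set to 0 from the date of death.

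The cost is plan wording and some analysis time, with no new data or participants. The downsides are reliance on a missing-at-random assumption and a less simple headline method. The model recovers nothing beyond the baseline score for participants lost before discharge. It also does not score deaths, which is why the counts must stand beside the estimates.

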Following esophagectomy or total gastrectomy patients often struggle to establish an adequate nutritional intake orally due to a combination of poor appetite, a fear of eating, early satiety, abnormal gut transit, gastrointestinal symptoms such as nausea, reflux, and altered bowel habits.

Studies have shown that over 60% of patients have an inadequate oral intake at time of hospital discharge, consuming 70 and 65% of their energy and protein requirements respectively [14]. An earlier study evaluating patients six months after esophagectomy demonstrated that 64% of patients reported a loss of greater than 10% of their baseline body mass index [15]. Estimates of the time taken to establish what would be considered a socially acceptable diet after surgery are around six months [16].

Weight loss and poor nutritional intake may contribute to the detrimental effect on overall quality of life (QoL) reported in these patients [17]. Although in general, tumor location and stage of disease are the major determinants of QoL, in esophageal cancer patient nutritional factors (dietary intake and weight loss) have been shown to be as important in determining functional QoL scores [18]. Global quality of life scores have been correlated with both postoperative BMI and weight loss [19].

Little is known about the patient experience of home tube feeding and studies often focus on heterogeneous populations of variable age and dependency [20]. In esophagogastric patients, the JEJ tube already remains in place but any additional effect of using it is not known. The effect on family and carers and their relationship to the patient must also be considered as home tube fed subjects are often reliant on support, and carers perceive QoL very differently to that of the patient [21,22]. This may increase the burden of treatment.

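### The lead QLQ-C30 effect estimate is an unadjusted t-test with a data-dependent switch, while the already planned ANCOVA, probably the more precise analysis, is ranked second

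*Protocol article*

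**What the plan says.** Under Data analysis, Quantitative data, the protocol article expects QoL to be the likely outcome of the definitive trial. It then states that the comparison of QLQ-C30 "will be conducted using the Students t-test to compare the mean between the groups to provide a preliminary estimate of the treatment effect". The next step depends on the data: "Distribution of the data will be assessed graphically and if the normality assumption is considered to be unreasonable a non-parametric approach will be taken". The adjusted model comes third in order: "A secondary analysis, using analysis of covariance (ANCOVA) and regression models will be conducted to adjust for type of surgery" and for the baseline QLQ-C30 score. The remaining QoL measures and continuous outcomes are to be handled in the same way.

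Both covariates are built into the design. The Randomization section describes allocation "using permuted block randomization, stratified for type of procedure (esophagectomy or total gastrectomy"), and says that participants are randomized "at enrolment, and prior to surgery, so that baseline QoL and nutritional parameters can be collected". Table 1 schedules the EORTC questionnaires at Visit 1.

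Two further statements limit the point. The same analysis section commits to calculating QoL variability within each arm and for the arms combined. The Outcome measures section names recruitment and retention, not QoL, as the primary outcomes.

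**The concern.** The purpose of the QoL analysis is estimation: an effect with a confidence interval, and quantities with which to size a larger trial. The estimate placed first uses neither the stratification factor nor the baseline score, although the trial has both and already plans to use them. If baseline score predicts follow-up score even moderately, the reader is given the wider of two available intervals as the main result. If procedure type is prognostic, a t-test that ignores it after stratified randomization also overstates the standard error.

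The switch is a separate weakness. It rests on a visual judgement with no criterion, made after the data are seen, in a trial whose research team knows the allocation. Because the same rule extends to the other outcomes, the lead method could differ between scales and visits, so the results would not share one estimand. A rank test used alone would give the lead comparison no mean difference, and the mean difference is the quantity a later sample size calculation would use.

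**Working it through.** **Inputs from the protocol.** 60 participants, 30 per arm, and up to 17% early withdrawal (Sample size); 95% confidence intervals (Data analysis); ANCOVA covariates of type of surgery and baseline score (Data analysis).

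**The plan's own figure.** 60 × (1 − 0.17) = 49.8, so the stated 50 completers reproduce (10/60 = 16.7%). This is taken as 25 per arm. The plan states no effect size, SD or power, so widths are given in SD units.

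**Assumptions.** The documents do not give the correlation r between baseline and follow-up QLQ-C30, so a range from 0 to 0.7 is shown. Procedure type is assumed to have no effect on the score.

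**Unadjusted t-test.** Half-width = t(0.975; 48) × √(2/25) = 0.569 SD.

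**ANCOVA, formula.** Half-width = t(0.975; 46) × √(2/25) × √(1 − r²). The two covariates reduce the degrees of freedom from 48 to 46. This formula ignores chance imbalance in the covariates and so is slightly optimistic.

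**ANCOVA, simulation.** To allow for that imbalance, 4,000 trials were simulated for each r, with 25 per arm, a continuous baseline and a binary stratum (assumed prevalence 25%). Entries are mean half-widths in SD units.

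| Assumed r | ANCOVA, formula | t-test, simulated | ANCOVA, simulated | Ratio, ANCOVA to t-test | Share of trials with narrower ANCOVA |
|---|---|---|---|---|---|
| 0 | 0.569 | 0.565 | 0.577 | 1.02 | 19% |
| 0.1 | 0.566 | 0.563 | 0.573 | 1.02 | 24% |
| 0.2 | 0.558 | 0.565 | 0.567 | 1.00 | 42% |
| 0.3 | 0.543 | 0.566 | 0.552 | 0.98 | 65% |
| 0.4 | 0.522 | 0.566 | 0.531 | 0.94 | 85% |
| 0.5 | 0.493 | 0.565 | 0.502 | 0.89 | 96% |
| 0.6 | 0.455 | 0.566 | 0.465 | 0.82 | 99% |
| 0.7 | 0.407 | 0.566 | 0.413 | 0.73 | 100% |

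**Reading.** Break-even is near r = 0.2. Below it, ANCOVA costs about 2% in width. Above it the gain grows: the unadjusted interval is about 13% wider at r = 0.5 (0.565/0.502 = 1.13) and about 37% wider at r = 0.7 (0.566/0.413 = 1.37). A prognostic effect of procedure type, set to zero here, would move the comparison further towards ANCOVA.

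**The case against.** The strongest reply is that both analyses are already planned, so the dispute is about which is listed first. The ANCOVA uses exactly the two covariates wanted and does not depend on the normality check. The QoL comparison is labelled preliminary in a pilot with feasibility outcomes, so no controlled error rate is at risk from a graphical choice. The gain also rests on an unknown correlation. Baseline is taken about two weeks before major surgery, so r could be modest, and at r = 0.3 the simulated gain is only about 2%. All of this stands. It limits the size of the point but does not justify ranking the unadjusted estimate first, because the possible loss from ANCOVA is about 2% and the possible gain much larger.

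The non-parametric method is not named. That detail may sit in the full protocol or analysis plan and is not counted here. The objection is to the switch itself.

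A reader might infer four stronger things that the protocol does not support:

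- **That the switch loses the variability estimates.** It does not: SDs by arm and pooled are promised whichever test is used.
- **That the trial may yield no mean difference.** The ANCOVA supplies one regardless. A non-parametric approach can also carry a location-shift estimate, or be a bootstrap of the mean difference.
- **That the Background proves the unadjusted interval too wide, because it says "tumor location and stage of disease are the major determinants of QoL".** That clause is a general statement, and the same sentence goes on to give nutritional factors equal weight in esophageal cancer. The stratification factor is procedure, not tumor location, and its prognostic strength is not reported.
- **That the definitive trial would be oversized by 1/(1 − r²), or 10% to 96% for r from 0.3 to 0.7.** This supposes a trial analyzed by ANCOVA but sized on the raw SD. The protocol does not say so, and the pilot's own ANCOVA data would allow the correction.

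**Conclusion.** The point holds in a limited form. The protocol draws its lead QLQ-C30 effect from an unadjusted t-test, with a change of method decided after looking at the data, and ranks the adjusted analysis second although the design supplies both covariates. With 25 completers per arm, the half-width is about 0.57 SD unadjusted, against about 0.55, 0.50 and 0.41 SD for ANCOVA at assumed correlations of 0.3, 0.5 and 0.7. There is no gain below about 0.2. These figures assume equal completion in the two arms and no effect of procedure type. The primary feasibility outcomes, the target of 60 and the stated withdrawal allowance are unaffected. This is a worthwhile improvement to a preliminary analysis; it does not threaten the pilot's validity.

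**What to change.** - Make the planned ANCOVA, adjusted for baseline score and type of surgery, the lead estimate for QLQ-C30 and for every other continuous outcome with a baseline value. Table 1 shows the food diary first at discharge, so nutritional intake would be adjusted for type of surgery only.
- Report the adjusted mean difference with its 95% confidence interval, the residual SD and the baseline-to-follow-up correlation. The last two let the definitive trial be sized for an adjusted analysis.
- Replace the graph-triggered switch with a sensitivity analysis fixed in advance that keeps the mean difference, for example a bootstrap confidence interval.
- Keep the unadjusted means, the SDs by arm and pooled, and the t-test as supportive results.

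The cost is a change of wording and two degrees of freedom in the lead model. No extra data, visits or participants are needed.
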